## Abstract

**Background/Objectives**: Older adults residing in long-term care frequently experience multimorbidity, low habitual activity, mobility decline, executive dysfunction, and reduced quality of life. Evidence separating the effects of exercise, cognitive stimulation, and their combination remains limited. The primary objective of this trial is to determine whether a 12-week combined physical exercise plus cognitive stimulation programme improves executive function, functional mobility, and health-related quality of life compared with usual care. Secondary objectives are to estimate the effects of each single-component programme, compare the combined programme with each component, and examine maintenance at six months. **Methods**: This is a four-arm, parallel-group, assessor-blinded randomised controlled trial in Portuguese long-term care facilities. A total of 140 residents aged 65 years or older, residing in long-term care for at least three months and able to provide informed consent, will be allocated 1:1:1:1 to supervised multicomponent exercise, group cognitive stimulation, combined exercise plus cognitive stimulation, or usual care. Active programmes will be delivered three times weekly for 12 weeks. Assessments are planned at baseline, post-intervention, and six-month follow-up according to the prespecified schedule. Primary outcomes are the Stroop interference score, Timed Up and Go time, and EQ-5D-5L index value at 12 weeks. Analyses will follow the intention-to-treat principle using mixed-effects models; multiplicity across the three primary endpoints will be controlled using Holm’s procedure, and interaction analyses will be exploratory and hypothesis-generating. **Results**: Recruitment and data collection had not started at manuscript submission; therefore, no participant data are reported. **Conclusions**: The trial will estimate the effects of the combined programme versus usual care and provide exploratory comparative evidence on the single-component programmes in real-world long-term care.

## 1. Introduction

Residents of long-term care facilities commonly experience accelerated functional and cognitive decline. Multimorbidity, polypharmacy, sedentary routines, and restricted opportunities for autonomous activity can reduce strength, balance, mobility, participation, and health-related quality of life. Executive abilities such as planning, inhibition, and divided attention are important for safe transfers, adapting gait, following daily routines, and engaging in meaningful activities. Decline in these domains is associated with greater dependence, falls risk, and poorer quality of life [1,2,3]. Participation in health-promoting activities also depends on the interaction between individual capability, motivation, social opportunity, and the physical environment, as emphasised by the COM-B framework and multidimensional active-ageing models [4,5]. Interventions must therefore be safe, accessible, motivating, compatible with facility routines, and sufficiently standardised for replication.

Supervised multicomponent physical exercise is a core non-pharmacological strategy for older adults. Programmes that combine balance, strength, flexibility, and functional mobility are consistent with international guidance and current geriatric exercise recommendations [6,7,8,9,10]. In long-term care, exercise can improve physical function and reduce factors associated with falls [2,3]. It may also support cognitive health through better vascular and metabolic function, sleep, mood, and brain plasticity [11,12,13]. These potential benefits are relevant where inactivity and limited environmental stimulation can accelerate both motor and cognitive decline.

Cognitive stimulation offers a complementary pathway through structured group activities involving attention, memory, executive control, language, orientation, calculation, and problem-solving. Such activities can support cognitive engagement and social interaction [14,15,16]. However, the strongest evidence for formal cognitive stimulation therapy concerns people with dementia [14,15]; evidence for group cognitive stimulation in older adults without a major neurocognitive disorder is smaller and partly extrapolated from cognitive-training research [16]. Testing this extrapolation is therefore an important purpose of the present trial. A combined physical-cognitive programme may target both motor capacity and executive control within the same care pathway [17,18].

Evidence on combined programmes remains heterogeneous in intervention dose, content, professional resources, outcomes, follow-up, and comparator definition. Trials of multicomponent exercise with simultaneous cognitive training suggest possible benefits in selected executive domains [19], while small pilot work integrating physical activity with mindful awareness supports feasibility but cannot establish comparative effectiveness [20]. Most studies compare one programme with usual care, so they cannot distinguish exercise effects from cognitive-stimulation effects or determine whether a combined programme adds benefit beyond either component. Complex behavioural interventions also make participant and provider blinding impracticable and create challenges for intervention fidelity, contact-time matching, and implementation [21]. The present four-arm design addresses these challenges through common eligibility and assessment procedures, blinded outcome assessment, standardised intervention manuals, component-specific fidelity records, and direct comparisons of exercise alone, cognitive stimulation alone, their combination, and usual care under the same facility conditions.

The primary objective is to determine whether a 12-week combined physical exercise plus cognitive stimulation programme improves executive function (Stroop interference score), functional mobility (Timed Up and Go time), and health-related quality of life (EQ-5D-5L index value) at 12 weeks compared with usual care. Secondary objectives are to estimate the effects of exercise and cognitive stimulation separately, compare the combined programme with each single-component programme, examine maintenance of selected outcomes at six months, and describe safety, adherence, and feasibility. The principal hypothesis is that the combined intervention will produce greater improvements than usual care across the three primary domains. Comparisons involving the single-component arms and formal interaction analyses are prespecified as exploratory and hypothesis-generating.

## 2. Materials and Methods

### 2.1. Trial Design, Setting, and Reporting Framework

This is a pragmatic, randomised, parallel-group, assessor-blinded, four-arm controlled trial with a 1:1:1:1 allocation ratio. Participants will be allocated to multicomponent physical exercise, cognitive stimulation, combined physical exercise plus cognitive stimulation, or usual care. Assessments are planned at baseline (T0), immediately after the 12-week intervention period (T1), and six months after programme completion (T2). The trial is designed to preserve ecological validity by delivering interventions on site within the participating long-term care facilities rather than in a laboratory or hospital environment.

The study will be conducted in four long-term care facilities (Estruturas Residenciais para Pessoas Idosas, ERPI units) operated by three non-profit private social solidarity providers in the district of Viseu, Portugal, in collaboration with Escola Superior de Saúde Jean Piaget de Viseu. One provider operates two of the participating ERPI units. Written institutional authorisation has been obtained from all four ERPI units. At the providers’ request, their identities are not reported in the public manuscript. The manuscript follows SPIRIT 2025 as the primary protocol-reporting framework, with CONSORT 2025 and TIDieR elements used where relevant [22,23,24]. The SPIRIT checklist, TIDieR intervention description, bilingual Portuguese-English participant information sheet and informed consent form, and a separate high-resolution planned CONSORT-style flow diagram are provided as supporting files.

### 2.2. Trial Status, Ethics, Registration, and Participant Consent

Participant screening, recruitment, and data collection had not started at the time of manuscript submission. Written institutional authorisation has been obtained from all four participating ERPI units. Accordingly, no participant flow, baseline data, or trial outcomes are reported. This protocol describes the planned trial design, intervention procedures, assessment framework, and analysis strategy. The planned participant pathway is summarised in Figure 1.

This study is being conducted as part of the Doctoral Programme in Health, Disability, Dependency and Well-being at the University of Salamanca, in collaboration with Escola Superior de Saúde Jean Piaget de Viseu and the InSIGHT Research Centre, Instituto Piaget, Portugal. Within this collaborative framework, the participant information sheet and informed consent form underwent official translation into Portuguese and back-translation to support linguistic and conceptual equivalence for their use in Portugal. The trial received prospective ethical approval from the Research Ethics Committee of the University of Salamanca (registry no. 1379; 20 May 2025). At the protocol-planning stage, the Ethics Committee of the Piaget Institute (CEIP), Portugal, was consulted regarding the need for an additional ethical review in Portugal and indicated that no further ethical review was required in view of the existing prospective ethical approval from the Research Ethics Committee of the University of Salamanca. Written institutional authorisation to conduct the study was obtained from each of the four participating ERPI units before recruitment. No resident was approached before institutional authorisation was completed, and recruitment and study procedures will be initiated in accordance with the approved protocol and site procedures. The study is registered at ClinicalTrials.gov (NCT07082504). All procedures will comply with the Declaration of Helsinki, applicable Portuguese requirements, and the General Data Protection Regulation [25,26].

Written informed consent will be obtained before baseline testing from participants with full decision-making capacity. Participants will be informed that participation is voluntary, that they may withdraw without penalty, and that withdrawal will not affect facility care. Eligibility and consent procedures will be implemented in collaboration with facility technical directors and nursing teams. Screening will use resident lists, available clinical records, staff referral, and routine institutional assessment of the capacity to understand the study information and follow instructions. No biological specimens will be collected. General study results will be communicated to participants and participating facilities according to participants’ preferences and institutional procedures.

### 2.3. Patient and Public Involvement

No patients or members of the public were formally involved in drafting the original protocol. Nevertheless, the intervention and assessment procedures were selected to be feasible within routine long-term care, and operational input from participating facilities informed scheduling, safety procedures, and the choice of group-based delivery. During trial implementation, practical feedback from residents and staff regarding acceptability, session burden, and logistical feasibility will be documented to inform interpretation and future scaling.

### 2.4. Participants and Recruitment

Potential participants will be residents of the participating long-term care facilities. Inclusion criteria are age 65 years or older; residence in the facility for more than three months; capacity to provide informed consent and understand the study instructions; sufficient Portuguese literacy to complete the Torga Stroop test; and willingness to complete the planned assessments and intervention procedures. Cognitive exclusions are a documented major neurocognitive disorder or other impairment that precludes valid consent or comprehension of instructions. Physical and safety exclusions are an acute medical condition, an unstable cardiovascular or respiratory condition, an unresolved injury following a recent fall, a recent fracture or surgery that makes exercise unsafe, or a physical or sensory impairment that prevents safe completion of study procedures despite reasonable adaptation. A recent fall alone will not exclude a resident because falls risk is clinically relevant to the target population; unresolved injury or medical instability will prompt temporary ineligibility and medical review. Nursing staff and a physiotherapist will complete a pre-exercise safety screen, and medical clearance will be requested whenever contraindications are uncertain.

Recruitment will be conducted within the facilities through staff referral and screening of resident lists. Eligible residents will receive oral and written study information. Baseline assessment will include sociodemographic and clinical variables, medication use, length of residence, recent falls and fractures, exercise contraindications, and standardised physical, cognitive, and psychosocial measures. The numbers screened, excluded, randomised, assessed after intervention, and assessed at follow-up will be documented to support transparent reporting of feasibility and retention.

Recruitment in long-term care is influenced by clinical instability, fluctuating motivation, family involvement, and the operational routines of each institution. For this reason, the trial emphasises local coordination and resident-centred communication rather than external recruitment campaigns. Facility staff may support the identification of residents who can be approached, but participation will remain a research decision made by each eligible resident after receiving study information. This process is intended to balance feasibility with respect for autonomy and to reduce the risk that the resident-care relationship could be perceived as pressure to participate.

### 2.5. Randomisation, Allocation Concealment, and Blinding

Randomisation will be performed only after eligibility confirmation, written consent, and completion of baseline assessment. Participants will be allocated 1:1:1:1 within each ERPI using computer-generated lists with randomly varying block sizes. An adjunct professor at Escola Superior de Saúde Jean Piaget de Viseu who has no role in recruitment, baseline or outcome assessment, intervention delivery, or data analysis will generate and hold the allocation sequence. The sequence will be stored in a password-protected file on an institutional computer accessible only to this custodian. After baseline data are confirmed as complete, the facility technical director will send the coded participant identifier to the custodian, who will reveal only that participant’s assignment through individual secure communication. Local staff will retain the revealed assignment and intervention schedule but will not have access to future allocations. Outcome assessors will remain blinded. These safeguards distinguish allocation concealment before assignment from assessor blinding after assignment.

Participants and intervention providers cannot be blinded because of the behavioural nature of the programmes. Outcome assessors will be blinded to group allocation and will conduct assessments using participant lists that include identifiers but not treatment assignment. Participants and staff will be reminded not to disclose intervention participation during assessments. Statistical analysis will use coded group labels until the primary analyses are complete.

Contamination is a realistic risk in residential facilities because residents share social spaces and may discuss activities. To mitigate this, interventions will be scheduled separately where feasible, provider teams will follow predefined procedures, and usual-care activities will be documented monthly. Baseline comparability and any material changes in routine activities will be reported transparently, and sensitivity analyses will consider potential clustering or contamination effects.

### 2.6. Interventions

All active interventions will be group-based, delivered face-to-face on site, and scheduled three times per week for 12 weeks. Attendance, protocol deviations, and relevant occurrences will be recorded. The combined arm will receive both intervention components during the same visit, which reflects a realistic multimodal delivery model but introduces greater contact time than the single-component arms; this issue will be considered when interpreting comparative effects.

Table 1 summarises the main intervention components. More detailed intervention reporting is provided in Supplementary Material S2.

#### 2.6.1. Physical Exercise Programme

The physical exercise programme is designed to improve balance, strength, aerobic endurance, flexibility, and functional mobility while minimising risk and preserving feasibility in long-term care. Each approximately 60-min session will include about 50 min of active exercise and 10 min for transitions and individualised rest: 5 min of joint mobility and seated or standing marching; 10 min of balance training; 20 min of resistance and functional-mobility exercises; 10 min of continuous or interval walking or seated stepping; and 5 min of cool-down, breathing, and flexibility. Balance tasks will include supported static and dynamic postures, progressive reductions in base of support, controlled weight shifts, stepping, turning, figure-of-eight walking, and obstacle negotiation when clinically appropriate [6,7,8,9,10].

Resistance and functional exercises will include sit-to-stand, knee extension, plantar flexion, hip abduction, upper-limb pulling or elbow flexion, and step practice using body weight, chairs, elastic bands, bottles, or ankle weights. Weeks 1–2 will begin with one set of 8–10 repetitions; weeks 3–6 will progress toward two sets of 8–12 repetitions; and weeks 7–12 may progress to two or three sets of 8–12 repetitions according to tolerance. Exercise will be tailored to baseline function while preserving the standardised session structure. Aerobic intensity will be maintained at a positive talk test, allowing complete sentences with some effort, and overall exertion will start at 2–3 and progress to 3–4 on the Borg category-ratio 10 scale (CR10) [27,28,29]. Progression will be reviewed every two weeks and implemented only after two consecutive sessions are completed with safe technique, Borg CR10 no higher than 3 at the current dose, an appropriate talk test, and no clinically relevant symptoms. Only one variable will be increased at a time: repetitions up to 12, then the smallest available resistance increment, task complexity, or aerobic duration. Sessions will be paused or discontinued for chest pain, marked breathlessness, dizziness, symptomatic hypotension, new or worsening pain, gait instability, or any clinically relevant change in well-being, followed by nursing or medical review according to facility procedures.

#### 2.6.2. Cognitive Stimulation Programme

The cognitive stimulation programme will consist of small-group sessions designed to stimulate executive and broader cognitive domains relevant to daily functioning. Activities will include structured games, riddles, puzzles, orientation tasks, reasoning exercises, inhibition tasks, memory activities, and paper-and-pencil exercises targeting attention, working memory, cognitive flexibility, language, and visuospatial skills [14,15,16].

Tasks will be adapted according to participants’ comprehension and performance, progressing from simpler to more complex activities over the intervention period. Group delivery is intended not only to stimulate cognition but also to reinforce social interaction, motivation, and adherence, which are central to sustainable long-term care programming.

#### 2.6.3. Combined Intervention and Concomitant Care

Participants in the combined arm will receive both programmes during the same visit, with exercise followed immediately by cognitive stimulation. Attendance will be recorded separately for each component so that delivered dose can be characterised accurately. The design reflects a clinically plausible multimodal intervention but also introduces higher weekly structured contact time than the single-component arms; this will be acknowledged explicitly when interpreting whether the combined arm performs better than either single-component arm.

Routine facility care, regular medication, and usual supportive services will be permitted in all groups. New structured physiotherapy or organised exercise/sport programmes outside the study interventions will be discouraged when feasible and, if they occur, documented for sensitivity analyses. Monthly logs completed by facility technical directors will record relevant co-interventions, new rehabilitation programmes, and material changes in routine activities.

### 2.7. Outcomes and Assessment Schedule

The three primary outcomes are assessed at 12 weeks (T1): functional mobility measured by Timed Up and Go (TUG) time, with dual-task TUG as a supportive measure [30,31]; executive function measured by the Torga Stroop inhibitory-control index (correctly read words per second minus correctly named incongruent colours per second; lower values indicate better inhibitory control) [32,33]; and health-related quality of life measured by the EQ-5D-5L index value derived from the Portuguese value set [34,35]. The EQ visual analogue scale (EQ-VAS) will be collected at the same visits as a supportive quality-of-life measure.

Secondary outcomes include balance assessed with the Performance-Oriented Mobility Assessment (POMA/Tinetti) [36]; lower- and upper-limb strength, flexibility, and aerobic endurance assessed using Senior Fitness Test components, with handgrip strength assessed by dynamometry (Baseline® Hydraulic Hand Dynamometer (Fabrication Enterprise Inc., Elmsford, NY, USA) [37]; global cognition measured by the Mini-Mental State Examination (MMSE) and complementary executive measures using the Trail Making Test (TMT) and Digit Span [38,39,40]; sleep quality measured by the Pittsburgh Sleep Quality Index (PSQI) [41,42]; depressive symptoms, life satisfaction, and psychological well-being measured by the Geriatric Depression Scale (GDS), Satisfaction With Life Scale (SWLS), and Psychological Well-Being Scales (PWBS) [43,44,45]; functional independence measured by the Barthel Index [46]; physical activity measured by the Global Physical Activity Questionnaire (GPAQ) and pedometer monitoring (three-axis digital pedometer (Walking Style One 2.1, HJ-321-E; OMRON HEALTHCARE Co., Ltd., Muko, Kyoto, Japan) [47,48]; and anthropometrics, vital signs, and selected sociodemographic and clinical variables. Blood pressure and resting heart rate will be measured using an automated upper-arm blood pressure monitor (OMRON M6 Comfort, HEM-7221-E; OMRON Healthcare Co., Ltd., Kyoto, Japan) and body mass will be measured using a digital scale (Seca 813; seca GmbH & Co. KG, Hamburg, Germany), and height using a portable stadiometer (Seca 213; seca GmbH & Co. KG, Hamburg, Germany.

### 2.8. Sample Size

The target sample size is 140 randomised participants (approximately 35 per arm). This is the pragmatic recruitment target rather than a zero-dropout analysable sample; loss of up to 20% by T1 is anticipated, leaving approximately 112 participants (28 per arm). The sample is feasibility-driven, reflecting the recruitment capacity of the participating facilities and intervention workload. The Torga validation study reported a standard deviation of 0.43 for its inhibitory-control index [33]. With 35 participants in the combined and usual-care arms, a two-sided independent comparison at alpha = 0.05 and 80% power has a minimum detectable difference of approximately 0.67 standard deviations, equivalent to 0.29 index points. If 20% are unavailable at T1 (28 per arm), the corresponding value is approximately 0.75 standard deviations or 0.32 index points. Baseline-adjusted mixed models may improve precision, but these conservative values make clear that the trial is designed to detect moderate-to-large rather than small effects.

The primary estimand is the adjusted between-group difference in change from baseline to T1 for the combined intervention versus usual care. This estimand will be evaluated for the Stroop interference score, TUG time, and EQ-5D-5L index. Effect estimates and 95% confidence intervals will be emphasised. Comparisons involving the exercise-only and cognitive-stimulation-only arms, maintenance at T2, and exercise-by-cognitive-stimulation interaction effects are exploratory because the pragmatic sample was not selected to power those tests.

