### 2.10. Statistical Analysis

Statistical analyses will be performed using IBM SPSS Statistics, version 32.0 (IBM Corp., Armonk, NY, USA). Analyses will follow the intention-to-treat principle, with all randomised participants analysed in their allocated groups regardless of adherence [49]. Baseline characteristics will be summarised using appropriate descriptive statistics. Mixed-effects models will estimate changes over time and group-by-time differences for each outcome distribution [50]. Models will include group, time, group-by-time interaction, baseline outcome value, and facility as a fixed effect or clustering factor, as supported by the number of participating facilities and model stability.

The primary family comprises the combined-intervention versus usual-care contrasts at T1 for the Stroop interference score, TUG time, and EQ-5D-5L index. The family-wise two-sided Type I error rate will be controlled at 0.05 using Holm’s step-down procedure. Secondary between-arm contrasts and secondary outcomes will be treated as exploratory; within prespecified outcome families and time points, false discovery rate will be controlled using the Benjamini–Hochberg procedure, with both unadjusted and adjusted p-values reported. Follow-up models will examine maintenance only for outcomes collected at T2. Supportive analyses may include per-protocol, adherence-informed, dose-response, and co-intervention-adjusted models. Multiple imputation may be used if missingness is non-trivial and the assumptions are defensible [51] (Table 4).

Results will be reported as adjusted mean differences or appropriate model-based contrasts with 95% confidence intervals. The direction of benefit will be stated explicitly. Adherence will be summarised by arm and component using sessions attended, percentage of planned sessions completed, and total minutes delivered. A factorial coding of exercise (present/absent) and cognitive stimulation (present/absent) will be used in an exploratory exercise-by-cognitive-stimulation-by-time model. Because the trial is not powered for interaction testing and the combined arm has greater contact time, these analyses will be described as hypothesis-generating and will not support confirmatory claims of synergy.

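### The minimum detectable differences in section 2.8 are computed at alpha 0.05 and called conservative, but the contrast is tested in a three-endpoint Holm family whose first threshold is 0.0167

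*Protocol article*

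**What the plan says.** Section 2.8 describes a sample set by feasibility and then states what it can detect for the combined versus usual-care contrast on the Stroop index. "With 35 participants in the combined and usual-care arms", it says, "a two-sided independent comparison at alpha = 0.05 and 80% power has a minimum detectable difference of approximately 0.67 standard deviations", which it converts to 0.29 index points using an SD of 0.43 from the validation study. It continues: "If 20% are unavailable at T1 (28 per arm), the corresponding value is approximately 0.75 standard deviations or 0.32 index points". It then notes that baseline adjustment may improve precision and concludes that "these conservative values make clear that the trial is designed to detect moderate-to-large rather than small effects".

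Section 2.10 places this contrast in a primary family with the matching Timed Up and Go and EQ-5D-5L contrasts. Of that family it says: "The family-wise two-sided Type I error rate will be controlled at 0.05 using" Holm's step-down procedure. Table 4 marks all three rows as Holm-adjusted. Section 2.8 mentions neither Holm nor any alpha below 0.05.

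**The concern.** The detectable difference and the planned test use different significance thresholds. Under Holm with three endpoints, the smallest p-value is compared with 0.05/3 = 0.0167, the next with 0.05/2 = 0.025, and the largest with 0.05. An endpoint gets the full 0.05 only after the other two have been rejected. The stated figures therefore describe the most favourable position an endpoint can have under Holm, and calling them conservative points the reader the other way.

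These are the only quantitative statements of what the trial can detect, and they concern its principal efficacy comparison. A reader who takes them at face value will credit the trial with 80% power at differences where its own decision rule gives less. A non-significant primary result would then be read as stronger evidence against an effect of that size than it is.

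**Working it through.** **Inputs.** From section 2.8: 35 per arm, or 28 per arm after 20% loss; two-sided alpha 0.05; power 80%; SD 0.43. From section 2.10: three endpoints, Holm, family-wise 0.05. The correlation between endpoints is not given, so 0, 0.3 and 0.5 are assumed.

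**Step 1: reproduce the plan's figures.** For two equal arms, by the normal approximation,

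MDD/SD = (z(1 − alpha/2) + z(0.80)) × √(2/n), with z(0.80) = 0.8416.

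At alpha 0.05, z(0.975) = 1.960, so the sum is 2.8016.

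- n = 35: 2.8016 × √(2/35) = 2.8016 × 0.2390 = 0.670 SD; × 0.43 = 0.288 points.
- n = 28: 2.8016 × √(2/28) = 2.8016 × 0.2673 = 0.749 SD; × 0.43 = 0.322 points.

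Both match the document.

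**Step 2: the same formula at each Holm threshold.** At 0.0167, z = 2.394 and the sum is 3.2356. At 0.025, z = 2.241 and the sum is 3.083.

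| Alpha | 35 per arm | 28 per arm |
|---|---|---|
| 0.05 (other two already rejected) | 0.670 SD, 0.288 points | 0.749 SD, 0.322 points |
| 0.025 (one other already rejected) | 0.737 SD, 0.317 points | 0.824 SD, 0.354 points |
| 0.0167 (none rejected yet) | 0.773 SD, 0.333 points | 0.865 SD, 0.372 points |

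The first-step values exceed the stated ones by 3.2356/2.8016 = 1.155, about 15%. With the noncentral t distribution, the 0.05 values are 0.679 and 0.762 SD and the 0.0167 values are 0.790 and 0.889 SD, so the gap is of similar size.

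**Step 3: power at the stated differences with alpha 0.0167.** Power = Φ(d × √(n/2) − 2.394).

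- d = 0.67, n = 35: Φ(2.803 − 2.394) = Φ(0.409) = 0.659.
- d = 0.75, n = 28: Φ(2.806 − 2.394) = Φ(0.412) = 0.660.

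The noncentral t gives 0.637 and 0.632.

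**Step 4: power under the whole Holm procedure.** This was simulated with 400,000 draws per scenario of three correlated normal test statistics, each responding endpoint having mean d × √(n/2). The two-sided p-values were ordered and compared with 0.0167, 0.025 and 0.05, stopping at the first failure. The probability that one given responding endpoint is rejected was:

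| Scenario | 35 per arm, 0.67 SD | 28 per arm, 0.75 SD |
|---|---|---|
| Only that endpoint responds | 0.659 to 0.661 | 0.661 |
| All three respond equally | 0.735 to 0.752 | 0.738 to 0.753 |

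Ranges are over the three assumed correlations. No scenario reaches 0.80.

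**Step 5: what baseline adjustment could recover.** If adjustment multiplies the variance by (1 − ρ²), where ρ is the baseline-to-T1 correlation, the first-step MDD returns to the stated value when √(1 − ρ²) = 2.8016/3.2356 = 0.866. That gives ρ = √(1 − 0.750) = 0.50, or 0.51 by noncentral t. By noncentral t, the first-step MDDs with 35 and 28 per arm are:

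- ρ = 0.3: 0.75 and 0.85 SD
- ρ = 0.5: 0.68 and 0.77 SD
- ρ = 0.7: 0.56 and 0.63 SD

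The document gives no value for ρ.

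**The case against.** The best defence is that section 2.8 makes no arithmetic error and hides nothing: the condition "a two-sided independent comparison at alpha = 0.05 and 80% power" is printed with the figure. This stands. The fault is that the condition is not the one the primary test will meet, and that the result is called conservative.

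The second defence is that the planned model adjusts for baseline, so its detectable difference may be smaller than any value tabulated here. This also stands in part. A correlation of about 0.5 would offset the whole first-step loss. But the document states no correlation, so a possible gain is being set against a known loss that goes unmentioned. The values are conservative in ignoring baseline adjustment; they are not conservative as to multiplicity.

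Third, Holm is step-down, so 0.77 and 0.86 SD are bounds and not the detectable difference in every case. This is right, and the fix labels them so. If all three endpoints respond equally at the stated size, the shortfall per endpoint is only about 5 to 6 percentage points, and at least one endpoint is rejected in 87 to 96% of trials.

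A reader might infer more than the document supports:

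- **That 140 is the wrong sample size.** Section 2.8 does not derive the number from this calculation.
- **That the trial has only about a 50 to 60% chance of meeting its hypothesis.** The introduction says: "The principal hypothesis is that the combined intervention will produce greater improvements than usual care across the three primary domains". The simulated chance that all three are rejected at the stated effects is indeed 50 to 60%. But three independent endpoints at 80% power with no correction give 0.8³ = 51%, against 50% under Holm, so that low figure comes almost entirely from requiring all three. Section 2.10 and Table 4 set no such requirement.
- **That the 95% intervals are wrong.** Section 2.8 says: "Effect estimates and 95% confidence intervals will be emphasised". Unadjusted intervals beside Holm-adjusted tests are ordinary practice, and Bonferroni intervals at 98.3% would not match Holm's decisions either.
- **That the effects must be relabelled as large.** The documents set no threshold, and moderate-to-large remains a fair description of 0.77 to 0.86 SD.

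**Conclusion.** The point holds as a mismatch between the stated power and the planned decision rule. The figures 0.67 and 0.75 SD are right for a single test at 0.05, but under Holm they are the favourable end of a range that reaches 0.77 and 0.86 SD. At the stated differences, power for one endpoint is about 66% if it alone responds and about 74 to 75% if all three respond equally, against the 80% printed.

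These powers assume a comparison without baseline adjustment, a normal approximation, and endpoint correlations of 0 to 0.5. Whether the planned adjusted model does better or worse than the printed figures cannot be settled from the document. The consequence is an overstated sensitivity statement; Type I error control, the analysis and the recruitment target are untouched.

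**What to change.** In section 2.8, keep the alpha 0.05 figures and label them as the most favourable case under Holm, reached when both other primary endpoints have been rejected. Beside them, report the first-step values: 0.77 SD (0.33 index points) with 35 per arm and 0.86 SD (0.37 index points) with 28 per arm. Label these as the bound that applies when no other endpoint has been rejected.

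Delete the word conservative, or limit it to the fact that the calculation ignores baseline adjustment. If the authors want to rely on that adjustment, they should state the baseline-to-T1 correlation they assume and give its source; about 0.5 is needed to offset the first Holm step.

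The cost is a few sentences and a less favourable stated sensitivity. The sample size, the endpoints, the Holm procedure and the models stay as they are. Recruitment had not started when the article was submitted.
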